#### **7.2.2. Parameters to be measured**

a. GMT, seroprotection and seroconversion rates before and after one dose of immunization will be described per antigen per group vaccine with 95% confidence interval (CI).

b.1 Local reactions and systemic events occurring within 30 minutes after vaccination, 72 hours after vaccination and unexpected event rates, which occurred after 72 hours will be assessed per antigen and per group vaccine with 95% CI.

Any Serious Adverse Events occurring over the study period will be described.

**Subjects** will record the presence of any local or systemic symptom within 28 days following each injection in the diary card. They will answer all questions in the diary for expected and unexpected events during this period.

**The investigator** will report the following data in the CRF:

- The start and end dates of all events.
- The severity (code 1, 2 or 3) of all local reactions.
- Site of local reactions.
- The severity (code 1, 2 or 3) of all systemic events.
- The exact daily maximal axillary temperature up to 3 days after the vaccination.
- The exact maximal axillary temperature of any other fever period.
- The action taken.

#### **b.2 Safety assessment:**

The investigator will assess the intensity (code 1, 2 or 3), duration and relation.

- Percentage of subjects with at least one immediate reaction (local reaction or systemic event) within 30 minutes after each vaccination.
  - Local and systemic reactions, expected or not, occurring within 72 hours after each injection will be evaluated by interviewing the subject/parents during the post surveillance visits: V0, V2 and V3. Particularly, the axillary temperature will be measured for three days after vaccination, in the evening and/or at time of febrile peak, and the highest temperature will be recorded in the diary
-

---

card, expressed as Celsius degrees, using a thermometer. The trial team will record the information in the CRF.

- Any serious adverse event occurring during the study.

### 8.1. Statistical Methods and Data Analysis

#### 8.1.1. Determination of Sample Size

##### 8.1.1.1. Proportion Formula

Sample size is determined based on 95% confidence interval and power of the test 80%. Using sample size formula for comparing two a population proportion

$$n = \frac{\left( Z_{1-\alpha/2} \sqrt{2\bar{P}(1-\bar{P})} + Z_{1-\beta} \sqrt{p_1(1-p_1) + p_2(1-p_2)} \right)^2}{(p_1 - p_2)^2}$$

with  $p_1$  = immunogenicity of Trivalent Influenza HA vaccine = 96% and the maximum difference between two proportion equal 15% (or  $p_2$  = immunogenicity of QIV = 81%), from the formula, the required sample size would be 115 in each group including 20 % of drop out anticipation

**8.1.1.2.** To evaluate immunogenicity and safety in three consecutive batches of quadrivalent Influenza HA vaccine in group 9-40 years of age. Sample size is determined based on formula for studies one proportion :

$$n = \frac{(Z_{1-\alpha/2} \sqrt{p_0(1-p_0)} + Z_{1-\beta} \sqrt{p_1(1-p_1)})^2}{(p_1 - p_0)^2}$$

With  $p_0$  = immunogenicity in each batches of quadrivalent = 0.96;  $(p_1 - p_0)$  = effect size, is determined at least 0.06 (or  $p_1$  equal 0.90). For 95% confident interval and power of the test 80% ( $Z_{1-\alpha/2} = 1.96$ ;  $Z_{1-\beta} = 0.84$ ), from the formula above, the estimated sample size is  $n = 112$  for each batches.

With the assumption that not all of the subject could complete the study, the total number of subject will be added at least 20%,  $(N \times 1.2) = 134$  from the minimum requirement. Approximately 135 subjects per group will be involved in this study.

Since using the second formula need more subjects, then for this study 135 subjects will be involved for each group, and totally 810 subjects for the whole study, with expectation the sample size will be suitable for both formulas.

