**There are two sub-studies in this protocol**

- **Sub Study A (Subjects 9 - 40 years of age) :**

To evaluate immunogenicity and safety of quadrivalent compare to trivalent Influenza HA vaccine and to **evaluate lot to lot consistency in three consecutive batches of quadrivalent Influenza HA vaccine**. This is an experimental, randomized, double blind bridging study.

Five hundred forty (540) subjects will be involved in this study. Each subject will receive one dose of quadrivalent influenza vaccine with different batch number (batch 1/batch 2/batch 3) or trivalent HA vaccine according to the randomization list. Each group consist of 180 subjects, @ 45 subjects will receive QIV batch 1/2/ 3 or TIV.

| Group          | Age           | Vaccine |      |      |     | Vaccine dose |
|----------------|---------------|---------|------|------|-----|--------------|
|                |               | QIV1    | QIV2 | QIV3 | TIV |              |
| I              | 9 – 12 years  | 45      | 45   | 45   | 45  | 0.5 ml       |
| II             | 13– 17 years  | 45      | 45   | 45   | 45  | 0.5 ml       |
| III            | 18 – 40 years | 45      | 45   | 45   | 45  | 0.5 ml       |
| Total Subjects |               | 135     | 135  | 135  | 135 | -            |

**The subject will be grouped into three different batch of Quadrivalent Influenza vaccine to evaluate lot to lot consistency batches.**

---

---

- **Sub Study B (Subjects 6 months - 8 years of age)**

This is an experimental, open labelled bridging study.

270 infants and children will be involved in this study. Each subject will receive two doses of influenza HA vaccine from one batch number.

| Group | Vaccine | Age         | Number of subjects |
|-------|---------|-------------|--------------------|
| IV    | 3070217 | 6-35 Months | 135                |
| V     | 3070217 | 3-8 Years   | 135                |

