### 7.2. Secondary Evaluation Criteria

#### 7.2.1. Definition of the Criteria

##### **Immunogenicity**

- a. Serological response to influenza HA vaccine: GMT, percentage of subjects with increasing antibody titer  $\geq 4$  times and or percentage of subjects with transition of seronegative to seropositive 28 days after the last dose of Influenza HA vaccine.
- b. Description of serological response between quadrivalent and trivalent influenza HA vaccine in subjects 9-40 years old.
- c. Description of serological response between each batch number of Quadrivalent Influenza HA vaccine in subjects 9 -40 years old.

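### The 80% power stated for the three-batch objective comes from a one-sample formula and does not apply to a comparison between batches at the stated 6-point difference

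*Protocol*

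**What the plan says.** Section 3.1 of the protocol gives Sub Study A (9 to 40 years) the aim to "evaluate lot to lot consistency in three consecutive batches of quadrivalent Influenza HA vaccine", and explains the three quadrivalent arms by that aim: "The subject will be grouped into three different batch of Quadrivalent Influenza vaccine to evaluate lot to lot consistency batches".

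Section 8.1.1.2 sizes this objective. It states: "Sample size is determined based on formula for studies one proportion". The inputs are "immunogenicity in each batches of quadrivalent = 0.96" and "effect size, is determined at least 0.06", so the alternative is 90%. The normal quantiles are 1.96 and 0.84, that is, two-sided 5% and 80% power. The result is 112 per batch. Multiplying by 1.2 for dropout gives 134, and 135 is adopted. Because this number exceeds the one from 8.1.1.1, it is applied to all six groups, which gives the total of 810.

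The planned batch analysis is descriptive. Section 7.2.1 lists "Description of serological response between each batch number of Quadrivalent Influenza HA vaccine in subjects 9 -40 years old". Section 8.1.3.2 gives rates with exact 95% intervals, geometric mean titres with 95% intervals, and a description between groups. The protocol states no test between batches, no test of a batch against 96%, and no equivalence margin.

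**The concern.** Lot-to-lot consistency is a statement about batches relative to each other. A one-sample formula answers a different question: whether a single batch departs from a fixed reference of 96%. No analysis in 8.1.3 asks that question. Once the reference is another batch, it has to be estimated too, and the variance of the comparison is more than twice what the formula allows under its null.

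The formula is also built to detect a difference, whereas a consistency conclusion needs a difference to be ruled out.

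The number matters because the batch calculation sets the group size for the whole trial. A reader who sees 80% power in 8.1.1.2 and then similar batch rates in the report could take the similarity as well-powered evidence of consistency. At the difference the protocol names, a true gap between two batches would be missed more often than found.

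**Working it through.** **Inputs, all from 8.1.1.2:** rates 0.96 and 0.90, difference 0.06, quantiles 1.96 and 0.84, 112 evaluable per batch, 135 enrolled. A 20% loss from 135 leaves 135 × 0.8 = 108, so 108 is shown as well.

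**1. The protocol's own figure.**
n = (1.96·√(0.96·0.04) + 0.84·√(0.90·0.10))² / 0.06²
= (0.3841 + 0.2520)² / 0.0036 = 0.4046 / 0.0036 = 112.4.
The stated 112 reproduces, and 112 × 1.2 = 134.4, hence 134 to 135. The power of this one-sample test at n = 112 is 79.9%. The arithmetic is therefore sound for the question the formula asks.

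**2. Two batches, same inputs.** This is the two-proportion formula that the protocol itself prints in 8.1.1.1 for quadrivalent against trivalent vaccine. The mean rate is 0.93.
n = (1.96·√(2·0.93·0.07) + 0.84·√(0.96·0.04 + 0.90·0.10))² / 0.06²
= (0.7072 + 0.3010)² / 0.0036 = 1.0165 / 0.0036 = 282.4, so 283 evaluable per batch.

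**3. Power of that comparison at the planned size.**
Power = Φ((0.06·√n − 0.7072) / 0.3583).

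| Evaluable per batch | Argument of Φ | Power | Exact enumeration of the same z test |
|---|---|---|---|
| 108 | −0.234 | 41% | 42% |
| 112 | −0.202 | 42% | 44% |
| 135 (no loss) | −0.028 | 49% | 50% |

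**4. The difference that 112 per batch can detect with 80% power.** Take 0.96 against 0.85, with mean rate 0.905:
argument = (0.11·√112 − 1.96·√(2·0.905·0.095)) / √(0.96·0.04 + 0.85·0.15)
= (1.1641 − 0.8128) / 0.4073 = 0.863, so power is 81%.
Solving for exactly 80% gives a difference of 10.9 points at 112, 11.2 at 108 and 9.7 at 135.

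**5. Illustration for a consistency claim.** The protocol sets no equivalence margin, so the margins here are assumptions. Suppose every batch is truly at 96% and the two-sided 95% interval for a difference must lie inside ±m. With 112 per batch, SE = √(2·0.0384/112) = 0.0262, and the chance of passing for one pair is 2Φ(m/SE − 1.96) − 1. The figures for all three pairs come from simulation.

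| Assumed margin | One pair | All three pairs |
|---|---|---|
| 6 points | 26% | about 9% |
| 10 points | 94% | about 81% |
| 15 points | over 99% | over 99% |

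The answer depends almost wholly on the margin, so no single figure describes the design until a margin is set.

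**The case against.** **The wording of the objective.** The secondary objective in 2.2 speaks of comparison for quadrivalent against trivalent vaccine, but for the batches only of evaluating immunogenicity and safety in each. The planned outputs are per-group rates with exact intervals and a description. Sizing each batch as a single proportion partly fits that plan, and no section plans a between-batch test or a finding of no difference. This stands, and it lowers the severity. It does not rescue the power statement: 3.1 does name consistency between lots, 8.1.1.2 attaches 80% power to the batch objective, and no planned analysis tests a batch against 96%.

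**Reading too much into the formula error.** A reader might infer that 80% power exists for no batch comparison at all. That is not so. At 112 per batch, 96% against 85% has 81% power, and 96% against 81% (the 15-point difference used in 8.1.1.1) has 95%. The failure is at the stated 6 points.

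**Treating 6 points as an equivalence margin.** A reader might conclude that the trial has about a 9% chance of showing consistency. The protocol uses 0.06 as the effect size of a one-sample test and never as a margin. The 9% is an illustration and cannot be reported as a property of the design.

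**The missing margin.** A margin and decision rule may well stand in a statistical analysis plan that is not shown here. Their absence is not the fault. The fault is the power figure that the protocol does state.

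**Conclusion.** The concern holds in a limited form. The 112 and 135 are calculated correctly, but the 80% power they are said to give for the batch objective belongs to a one-sample test that the protocol does not plan. For two batches at 96% and 90%, power is about 41 to 42% at 108 to 112 evaluable per batch and 49% with no losses. To reach 80%, either 283 per batch or a true difference of about 11 points is needed. These figures assume the protocol's own rates, a two-sided 5% level, the pooled z test, one pair of batches and one strain, with no allowance for several pairs or strains.

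The documents do not support the further inference that the trial is too small and must grow to 283 per batch. The batch objective is secondary, its analysis is descriptive, and the primary seroprotection estimate is untouched. This is a correction that should be made, not one on which the trial's main result depends.

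**What to change.** Keep 135 per batch.

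1. In 8.1.1.2, remove the 80% power claim for the batch objective. Alternatively, restate it: with 108 to 112 evaluable per batch, power is about 41 to 42% to detect 96% against 90% between two batches, and reaches about 80% only near an 11-point difference.
2. Reconcile the lot-consistency aim in 3.1 with the descriptive analysis in 7.2.1 and 8.1.3.2. If the analysis stays descriptive, say in the protocol that a lack of observed difference between batches will not be reported as shown consistency.
3. If the sponsor wants a consistency conclusion, base it on confidence intervals for between-batch differences or geometric mean titre ratios against a margin fixed in advance. Give the probability of passing for all four strains over a range of standard deviations and margins, each labelled as an assumption.

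A range is needed because the protocol gives no standard deviation for log titres. Back-calculating from the 2008 trivalent results in section 1.5, with log-normal titres, gives about 0.45 to 0.54 log10, or about 0.53 to 0.62 if two-fold dilution steps are allowed for. With 108 per batch, identical batches and an assumed two-fold margin, the chance that all three pairs of one strain pass falls from 99% at 0.45 to 78% at 0.61. If all four strains must pass and are taken as independent, that 78% becomes 0.78⁴, or about 37%.

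The cost is wording in the protocol and, for item 3, in the statistical analysis plan. No further subjects are needed. The stated power becomes less favourable.

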#### 8.1.2. Data sets to be analyzed

##### 8.1.2.1. Definition of the population

---

---

**“Full Analysis Set” (Intention To Treat, ITT):** Every subject included in the study will be analyzed in this population, except if he/she did not receive any injection of one of the study vaccines.

**“Per Protocol Subjects” (PP):** Following non compliant subjects will be excluded from this population:

- Subjects included without meeting at least one inclusion criterion
- Subjects included despite meeting at least one non inclusion criterion
- Subjects found non compliant with the immunization or blood sampling schedule.
- Subjects vaccinated at least once with the wrong vaccine (non compliance with the randomization schedule).
- Subjects excluded from the ITT analysis.

### **8.1.2.2. Populations used in the analysis**

#### Safety Analysis:

All included and vaccinated subjects will be analyzed, each subject being analyzed according to the vaccine effectively received.

#### Immunogenicity Analysis:

The primary immunogenicity analysis will be conducted on the Per Protocol population. The secondary immunogenicity analysis will be conducted on the All Randomized population, each subject being analyzed according to the group attributed by the randomization process.

### **8.1.3. Statistical Methodology**

#### **8.1.3.1. Primary Criterion**

The main objective of the study is the protectivity rate of the Influenza HA vaccine. Percentage of subjects with anti Influenza titer  $\geq 1:40$  HI units 28 days after last injection.

#### **8.1.3.2. Secondary Criteria**

##### **Immunogenicity analysis**

- ◆ Seroprotection and seroconversion rates at last visit (V2 or V3 ): the following parameters will be presented: crude rates with their 95% confidence intervals (computed using the exact binomial probability)
  - ◆ Geometric means of titers (GMTs) with their 95% CI will be presented at V0 and V2 or V3.
-

- 
- ◆ Description between groups.

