## **1.5 Previous Study**

Bio Farma conducted several study for seasonal trivalent influenza vaccine but no for quadrivalent influenza vaccine.

From August to November 2008, a total of 405 adolescents and adults were enrolled for this bridging study of seasonal influenza HA vaccine (formulated in Bio Farma). The vaccine induced high antibody titers against influenza antigens in adolescent and adults, the percentage of subjects with anti-influenza titer  $\geq 1:40$  HI units to A/Hiroshima, A/Solomon Island and B/Malaysia strain were not different (97.8%; 98.2%, and 95.5%, respectively;  $p=0.025$ ). The Geometric Mean Titer (GMT) after immunization were increased (A/Hiroshima, GMT: 66.16 to 323.37; A/Solomon Islands, GMT: 41.89 to 554.26; and B/Malaysia, GMT: 24.02 to 231.83). Percentage of subjects with increasing antibody titer  $> 4$  times of anti A/Hiroshima, A/Solomon, and B/Malaysia were: 61.2%; 85.5%; and 81.5%, respectively. The percentage of subjects with transition of seronegative to seropositive of anti A/Hiroshima, A/Solomon, and B/Malaysia were 93.7%, 95.8%, and 93.9%, respectively. There were 81 (20.0%) who reported with local reaction and 16.3% who reported with

---

---

systemic reaction. All vaccines were well-tolerated and no serious adverse events during the study.

A yearly licensing study was conducted in 2010. From January to February 2010, a total of 60 adolescents and adults were enrolled for yearly licensing study (Phase IV). The percentage of subjects with anti-influenza titer  $\geq 1:40$  HI units to A/Brisbane/59/2007 (H1N1), A/Uruguay/716/2007 (H3N2), and B/Brisbane/60/2008 strain were high (100.0%; 100.0%, and 100.0%, respectively;  $p=1.000$ ). The GMT of anti A/Brisbane/59/2007 (H1N1), A/Uruguay/716/2007 (H3N2), and B/Brisbane/60/2008 titers 28 days after immunization was 738.5 HI units; 420.0 HI units; and 264.3 HI units, respectively. Percentage of subjects with increasing antibody titer  $> 4$  times, 28 days after immunization of anti to A/Brisbane/59/2007 (H1N1), A/Uruguay/716/2007 (H3N2), and B/Brisbane/60/2008 were: 75.8%; 84.5%; and 77.6%, respectively. The percentage of subjects with transition of seronegative to seropositive of anti to A/Brisbane/59/2007 (H1N1), A/Uruguay/716/2007 (H3N2), and B/Brisbane/60/2008 were 100.0%; 100.0%, and 100.0%, respectively. All vaccines were well-tolerated. There were no serious adverse events reported during the study.

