A similar study was conducted in 2011. Healthy adolescents and adults (12–61) years were assigned to receive one dose (0.5 ml) intramuscular injection of trivalent recombinant hemagglutinin containing H1, H3 and B antigens (Ag) derived from 2009 to 2010 influenza virus strains A/California/7/2009 (H1N1), A/Victoria/210/2009 (H3N2), B/Brisbane/60/2008. From January to February 2011, a total of 61 adolescents and adults were enrolled. The vaccine induced high antibody titers against influenza antigens in adolescents and adults, the percentage of subjects with anti-influenza titer  $\geq 1:40$  HI units to A/California/7/2009 (H1N1), A/Victoria/210/2009 (H3N2), B/Brisbane/60/2008 strain were not different (100.0%; 100.0%, and 100.0%, respectively;  $p=1.00$ ). The Geometric Mean Titer (GMT) after

---

---

---

immunization were increased (A/California/7/2009 (H1N1), GMT: 23.24 to 394.00; A/Victoria/210/2009 (H3N2), GMT: 44.90 to 394.37; and B/Brisbane/60/2008, GMT: 34.03 to 269.09). Percentage of subjects with increasing antibody titer > 4 times, 28 days after immunization of anti A/California/7/2009 (H1N1), A/Victoria/210/2009 (H3N2), B/Brisbane/60/2008 were: 93.3%; 80.0%; and 78.3%, respectively. The percentage of subjects with transition of seronegative to seropositive of anti A/California/7/2009 (H1N1), A/Victoria/210/2009 (H3N2), B/Brisbane/60/2008 were 100.0%, 100.0%, and 100.0%, respectively. All vaccines were well-tolerated.

A study using influenza vaccine produced by Biken institute was conducted in 2005 to children < 4 years of age. 259 children were involved received 2 doses of vaccines with the interval 4 weeks. Seroprotection were achieved by 23-42% in 0 year old, 49- 58% in 1 year old, 67-89% in 2 years old and 71-85% in 3 years old children. Immune response against influenza vaccine was highly influenced by prevaccination antibody levels and age.

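### Sub-study A compares batches, and QIV with TIV, by description only; state a GMT ratio with 95% CI per strain, adjusted for baseline titre and age group, because the ≥1:40 rate is near its ceiling

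*Protocol*

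**What the plan says.** Section 3.1 gives randomised, double-blind Sub-study A two comparative aims: QIV against TIV, and to "evaluate lot to lot consistency in three consecutive batches of quadrivalent Influenza HA vaccine". Section 2.2 lists both as secondary objectives.

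The analysis text does not carry these aims into a comparison. Section 7.2.1 lists, for batches, a "Description of serological response between each batch number of Quadrivalent Influenza HA vaccine in subjects 9 -40 years old", and words the QIV–TIV item the same way. Section 8.1.3.2 plans seroprotection and seroconversion as "crude rates with their 95% confidence intervals (computed using the exact binomial probability"). It adds "Geometric means of titers (GMTs) with their 95% CI will be presented at V0 and V2 or V3" and closes with "Description between groups". Section 7.2.2 asks for GMT, seroprotection and seroconversion per antigen and vaccine group with 95% CI. No section names a difference or ratio between groups.

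Age is built into the design: "Each group consist of 180 subjects, @ 45 subjects will receive QIV batch 1/2/ 3 or TIV". Titres are measured before vaccination in every subject (sections 3.4.4 and 7.1.3).

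**The concern.** Estimates for each group do not by themselves compare groups. A reader left with four rates and four GMTs per strain must judge consistency by eye, and whether two intervals overlap is a poor substitute for an interval on the contrast.

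The rate is also a blunt measure here. Section 1.5 reports ≥1:40 rates after vaccination of 97.8%, 98.2% and 95.5% in 2008, and 100% for every strain in 2010 and 2011. In 2008 one strain's titres were high before vaccination: "A/Hiroshima, GMT: 66.16 to 323.37", a baseline GMT already above 40. When nearly everyone clears the threshold, a real fall in titre moves few subjects below it.

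At stake is whether the trial can say anything precise about its two randomised questions, using data it already collects.

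**Working it through.** **The plan's own figure.** Section 8.1.1.2 sizes each batch on the rate, 0.96 against 0.90, with a one-proportion formula: (1.96·√(0.96·0.04) + 0.84·√(0.90·0.10))² / 0.06² = 112.4. This reproduces the stated 112; ×1.2 gives 134, rounded to 135. The formula compares one batch with a fixed value. Comparing two batches of 112 at 0.96 and 0.90 has about 42% power, and 80% would need 283 per batch.

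**Inputs.** Post-vaccination GMTs and ≥1:40 rates come from the 2008 study (section 1.5). Evaluable subjects per batch are 112 by the protocol's arithmetic, or 108 if exactly 20% of 135 are lost. The protocol gives no titre SD, so log-normal titres are assumed.

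**Formulas**, for a batch whose GMT is lower by a factor f:
- SD = log10(GMT/40) / z(rate). For A/Hiroshima: 0.908 / 2.014 = 0.451.
- Lower batch's rate = Φ(log10(GMT/(40f)) / SD).
- Power on the rate: two-sided 5% two-proportion z test.
- Power of the unadjusted GMT ratio = Φ(log10 f / (SD·√(2/n)) − 1.96).
- Probability that the two GMT intervals separate = Φ(log10 f / (SD·√(2/n)) − 1.96·√2).

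**Half the GMT (f = 2)**

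| Strain | SD, log10 | ≥1:40 rate | Power on rate, n = 108 / 112 | Power of GMT ratio, n = 108 / 112 | GMT intervals separate, n = 112 |
|---|---|---|---|---|---|
| A/Hiroshima | 0.451 | 97.8 → 91.1% | 58 / 59% | 99.8 / 99.9% | 99% |
| A/Solomon Islands | 0.544 | 98.2 → 93.9% | 37 / 38% | 98.2 / 98.5% | 91% |
| B/Malaysia | 0.450 | 95.5 → 84.8% | 76 / 77% | 99.8 / 99.9% | 99% |

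**GMT lower by a factor of 1.5**

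| Strain | Power on rate, n = 108 / 112 | Power of GMT ratio, n = 108 / 112 | GMT intervals separate, n = 108 / 112 |
|---|---|---|---|
| A/Hiroshima | 22 / 22% | 82 / 83% | 54 / 56% |
| A/Solomon Islands | 14 / 15% | 66 / 68% | 35 / 36% |
| B/Malaysia | 31 / 32% | 82 / 83% | 54 / 56% |

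**Sensitivity.** Titres come in two-fold steps, so the cut on the underlying scale may be nearer 28.3 than 40. With that cut, for a halved GMT at 112 per batch, power on the rate is 45%, 30% and 60%, and power of the ratio is 96–99%.

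**What adjustment adds.** With baseline correlation r, the residual SD is SD·√(1 − r²). At SD 0.451 and n = 112, the 95% CI of the ratio extends by a factor 10^(1.96·SD·√(1 − r²)·√(2/112)): 1.31 for r = 0, 1.27 for r = 0.5 and 1.24 for r = 0.6. The correlation is an assumption; the protocol gives none.

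**The case against.** The strongest reply is that the rate is only one planned readout. GMTs with intervals and ≥4-fold-rise rates are also reported by group. For a halved titre, the GMT intervals separate in about 91–99% of trials at 112 per batch. The 4-fold-rise rate detects it with 90–100% power, or 57–79% if the effective cut is 2.83-fold. This stands. A reader might infer that a batch with half the titre would pass unnoticed under the plan; that is true of the ≥1:40 rate, not of the plan as a whole.

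Three other tempting readings also fail:
- That baseline and age are ignored. The 4-fold rise uses the baseline titre, and age is balanced at 45 per cell.
- That unadjusted comparisons are biased. Under randomisation they are not; adjustment adds precision and removes the effect of chance imbalance in the sample obtained.
- That the protocol shows baseline and age to be prognostic at 9–40 years. The sentence "Immune response against influenza vaccine was highly influenced by prevaccination antibody levels and age" summarises a study of another manufacturer's vaccine in children under four, so it supports the covariates without proving them here.

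It may also be said that covariates belong in an SAP, which is not shown. That is fair: the absence of a covariate list is not the defect, and the text calls only the rates crude. But the protocol does fix description as the between-group analysis, while section 3.1 sets comparative aims.

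**Conclusion.** The point holds in limited form. The two randomised questions of Sub-study A have no stated effect measure, and the measure that drives the sample size is nearly saturated. On that rate, a halved GMT is detected with about 37–77% power. The planned GMT intervals cover that case well but separate for a 1.5-fold difference in only about 35–56% of trials, against 66–83% power for a direct ratio.

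Most of the gain therefore comes from stating the ratio; adjustment gives a modest further narrowing. The figures assume log-normal titres and take their SDs from earlier trivalent strains, so they are ranges, not predictions. Power to detect a difference is not evidence of consistency: without a margin, the ratio alone cannot establish it. The primary criterion is unaffected. This is a worthwhile, inexpensive improvement to a secondary analysis.

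**What to change.** In section 8.1.3.2, for immunogenicity in Sub-study A, replace the closing descriptive item with a stated contrast, and align items b and c of section 7.2.1:
- For each strain, fit ANCOVA of log10 post-vaccination titre on batch (or vaccine), log10 pre-vaccination titre and age group (I/II/III).
- Report the adjusted GMT ratio with 95% CI for the three batch pairs.
- Report the same ratio for pooled QIV against TIV on the three shared strains. Report B/Phuket separately, because TIV does not contain it (section 4.2.2).
- Give differences in the ≥1:40 rate, stratified by age group, as supportive.
- If a conclusion of lot consistency is intended, state the margin for the ratio beforehand; otherwise describe the result as an estimate.

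The cost is protocol or SAP wording and a standard model per strain. No new data are needed, and the primary criterion and visit schedule do not change.
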